## Abstract

**Background:**

Implant placement in the posterior maxilla is often complicated by the insufficient bone volume. While transalveolar sinus floor elevation (TSFE) has been proven as a predictable surgical procedure to increase the bone height in the posterior maxilla, questions in regard to the necessity of the bone grafting during the sinus lift and the question of whether TSFE could be performed when the residual bone height is below 5 mm are still debated. Furthermore, high-quality evidence comparing the clinical outcome of transalveolar sinus floor elevation with osteotome and modified sinus floor elevation with crestal non-cutting drills is limited.

**Methods/design:**

One hundred twenty adult patients who fit the inclusion criteria are being recruited from the Peking University Hospital of Stomatology First Clinical Division (Beijing, China). All patients are assigned to one of four groups according to a table of random numbers. Participants will receive (1) TSFE using osteotomes with bone grafting, (2) TSFE using osteotomes without bone grafting, (3) modified TSFE with bone grafting, or (4) modified TSFE without bone grafting. In a one-year follow-up period, implant survival rates, complications, implant stability, bone remodeling around the implant, and patient-reported outcome (visual analog scale for intraoperative discomfort and postoperative pain) will be observed and documented. The implant stability will be gauged by the resonance frequency analysis six times (at baseline and weeks 6, 8, 12, 16, and 26), and the bone remodeling will be observed and compared via radiographic examinations.

**Discussion:**

The result of the trial will potentially contribute to better decision making in atrophic posterior maxilla when implant placement is needed. Therefore, if the outcome is deemed favorable, the use of the modified TSFE would achieve an outcome equivalent to that of the traditional TSFE while introducing less trauma and postoperative discomforts. Separately, whether the bone graft procedure is necessary for the TSFE will also be discussed.

**Trial registration:**

The study has been registered in ClinicalTrials.gov under the identifier number NCT03445039. Registered on 26 February 2018.

**Electronic supplementary material:**

The online version of this article (10.1186/s13063-018-2879-x) contains supplementary material, which is available to authorized users.

## Background

When placing implants in the posterior maxilla, the dentist could often face the challenge of insufficient bone volume or poor bone quality or both [1–3]. Some efforts have been made to ensure successful implant treatment in the atrophic posterior maxillae. Sinus floor elevation has been proven to be a predictable surgical procedure to increase the bone height in the posterior maxilla which can be accomplished either through transalveolar sinus floor elevation or through a lateral window technique [4–7]. The transalveolar sinus floor elevation (TSFE) described by Summers in 1994 has been proven to be a predictable surgical procedure to increase bone volume in atrophic maxilla vertically [5, 6]. The original procedure is indicated when the residual volume of alveolar bone is between 4 and 8 mm below the sinus floor and the sinus membrane is elevated with osteotomes of increasing diameter from a crestal approach through the osteotomy prepared for dental implant placement but without need for a lateral window [5, 6].

Compared with the lateral sinus floor elevation (LSFE), the transcrestal sinus floor elevation technique has the advantages of limited trauma, bleeding, and swelling [8]. However, unlike LSFE, the surgical procedure in the TSFE is a visually restrictive technique, which makes it a technique-sensitive procedure, especially when direct visual examination of the sinus membrane is required. Furthermore, the bone height which could be augmented by the osteotomes is limited when compared with the lateral window technique [9].

Some studies reported a relatively high incidence of sinus membrane perforations when TSFE is performed [10]. Thus, some scholars have suggested modifying the operation procedure to reduce the incidence of the membrane perforation and increase the height of the membrane elevation. The methods of hydraulic pressure techniques, crestal non-cutting drills, and piezoelectric equipment have already been introduced to this field and achieved nearly ideal clinical outcomes [11–14].

The crestal non-cutting drills were designed in a dome-like shape, which could remove or push the residual cortical bone gently into the sinus without damaging the membrane. Furthermore, the specially designed instruments similar to the instruments for LSFE were used to elevate the membrane gently through the implant bed [13]. Thus, the membrane could be elevated in a more comfortable and gentle way. Because this technique does not involve the use of osteotomes and mallet, discomfort in patients can be reduced compared with conventional osteotome techniques [15]. Besides, the necessity of the application of the grafting material as bone substitute during the TSFE procedure is still under debate. According to Summers’s original publications, grafting material is recommended to be added into the elevation area [5, 6]. In a classic systemic review which was published in 2008, the author also mentioned that while performing transalveolar sinus floor elevation by using osteotome techniques, clinicians are advised to apply grafting materials to maintain the necessary spaces between the Schneiderian membrane and the floor of the sinus for bone regeneration [2, 3]. Furthermore, a series of studies have attempted to investigate the bone remodeling pattern after the TSFE and suggested that the TSFE with bone grafting could achieve more favorable results in bone remodeling when compared with TSFE without bone grafting [16]. However, several recent studies have reported that ideal clinical outcomes could be achieved when applying TSFE without bone grafting [1, 17–23]. In these studies, high implant survival rate and satisfying endo-sinus bone regeneration were found although the bone graft material was not applied. Thus, such a method was considered to be equally predictable as the TSFE with bone grafting [1, 19, 21]. Besides, spontaneous novo-bone formation could be found in these studies in which the bone grafting procedure was not performed [18, 19, 23]. Therefore, it is worthwhile to evaluate and compare the clinical results of the TSFE with different surgical protocols with or without bone grafting.

### Objectives and hypotheses

The major goals of the current randomized controlled trial are to compare and evaluate the clinical outcomes of the TSFE with different surgical protocols of patients with moderate insufficient vertical bone height (residual bone height is 3–6 mm).

The primary hypotheses are (1) the modified TSFE could achieve ideal clinical results similar to the traditional TSFE but with less patient discomfort and (2) TSFE with or without bone grafting can achieve ideal clinical results. The implant survival rate, complications, marginal bone remodeling, resonance frequency analysis measurements, and patient-reported outcome (visual analog scale, or VAS) for post-operative discomfort and pain will also be considered.

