### Primary parameters of the trial

The primary parameters of the current trial are implant survival rate, implant stability, and the bone remodeling around the implant.

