### Sample size

The sample size of the current trial is calculated based on the formula: *n* = 2(t_α_ + t_1-β_)^2^σ^2^/δ^2^. According to the preliminary experiment results and data analysis from currently published articles, the difference of the bone remodeling with and without bone grafting groups (δ) is around 0.8 mm, the difference of the bone remodeling between the original TSFE groups and modified TSFE groups is around 0.5 mm, and the standard deviation in groups (σ) is around 1 mm.

Thus, if the inspection level (α) is set at 0.05 and the power of test (β) is set at 90%, then 27 participants will be required for each group. Given a loss to follow-up rate of around 10%, the study would be anticipated to require 30 participants for each group. As a result, this trial will require at least 120 participants in its current setup.

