### Statistical analysis

For any continuous data (such as residual bone height or marginal bone remodeling), the inter-examiner agreement between the two examiners will be tested by the intra-class correlation coefficient. For the descriptive data, the inter-examiner agreement will be tested by the Cohen’s κ statistics.

The descriptive data will be expressed in absolute or relative percentage forms, and differences between the two subgroups will be analyzed by chi-squared test. The continuous data will be represented by mean and standard deviations, and the difference between the groups will be tested by analysis of variance (ANOVA).

In order to avoid the interference of measurement metrics due to having two main factors (surgical methods and bone grafting) in the current study, groups that are identical on individual aspects will be combined to discover the influence on the primary results by surgical method and bone grafting, respectively. For the surgical methods, results will be compared between the combined groups 1 + 2 and 3 + 4, whereas for the bone grafting, results will be compared between the combined groups 1 + 3 and 2 + 4. The difference between the groups will be tested by unpaired *t* test.

The statistical significance difference will be set as a *P* value of less than 0.05. All data analyses will be performed by SPSS statistical software .

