## Discussion

Although the transalveolar sinus floor elevation with osteotome has been proven efficacious in managing moderate vertical deficiencies in the posterior maxilla, questions as to the indication of the technique and necessity of the bone substitute are still under debated. Besides, certain studies have indicated that percussive forces of tapping by mallet provoke noise, or even bad feelings, and vibration in patients or can even give rise to vertigo in severe cases.

This study thus intends to explore whether the modified TSFE could achieve the same ideal clinical effect with less trauma and less complications. The necessity of filling the bone substitute during the TSFE will also be studied. We believe that this information could lead to an advanced treatment strategy of the TSFE with ideal clinical outcome.

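### For surgical technique the plan hypothesises similar results and foresees an equivalence conclusion, but it provides only tests of difference and no margin or confidence-interval rule that could support one

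*Protocol article*

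**What the plan says.** Objectives and hypotheses states as the first primary hypothesis that "the modified TSFE could achieve ideal clinical results similar to the traditional TSFE but with less patient discomfort". The Discussion part of the abstract says that, with a favorable outcome, "the use of the modified TSFE would achieve an outcome equivalent to that of the traditional TSFE". The main Discussion describes the aim as to "explore whether the modified TSFE could achieve the same ideal clinical effect with less trauma and less complications".

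The outcomes are set under Primary parameters of the trial: "The primary parameters of the current trial are implant survival rate, implant stability, and the bone remodeling around the implant".

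The inference is set under Statistical analysis. Categorical data get a chi-squared test. For continuous data, "the difference between the groups will be tested by analysis of variance (ANOVA"). For technique, "For the surgical methods, results will be compared between the combined groups 1 + 2 and 3 + 4", and "The difference between the groups will be tested by unpaired" *t* test. Significance is P < 0.05 throughout.

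Sample size uses a formula for detecting a difference. It cites about 0.8 mm for grafting and an SD of about 1 mm, and adds that "the difference of the bone remodeling between the original TSFE groups and modified TSFE groups is around 0.5 mm".

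**The concern.** A test of difference takes no difference as its null hypothesis. Failing to reject that null does not show that two techniques are alike, because the same result arises when the trial is too small or the measurement too noisy. A claim of similarity needs a stated limit on how far apart the techniques may be, and an interval estimate that falls inside it. The protocol has neither.

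The incentive also runs the wrong way: dropout and measurement error both make a non-significant result more likely. The Challenges section itself warns that the sinus floor border will sometimes be hard to see on the follow-up radiographs. At stake is the similarity half of the first primary hypothesis, and with it the main conclusion foreseen for the modified technique.

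**Working it through.** **Inputs from Sample size.** SD 1 mm; differences 0.8 mm (grafting) and 0.5 mm (technique); α 0.05; power 90%; 27 per group, 30 after 10% loss, 120 in total. The technique contrast pools two groups per side: 2 × 27 = 54 evaluable of 2 × 30 = 60 randomised.

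**The plan's own figure.** n = 2(z_α + z_power)²σ²/δ².
- δ = 0.8, one-sided α: 2(1.645 + 1.282)²/0.64 = 26.8, so 27. Then 27/0.9 = 30, and 4 × 30 = 120. This reproduces.
- δ = 0.8, two-sided α: 32.8, so 33. This does not reproduce.
- δ = 0.5: 69 (one-sided) or 85 (two-sided).

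So 27 per group comes from the 0.8 mm grafting difference with a one-sided α. The 0.5 mm figure does not drive it, and it is an expected difference, not a margin.

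**Two values for the SD.** If the 0.8 mm grafting effect is present and additive, each pooled technique arm is half grafted and half not. An unadjusted pooled *t* test then sees a variance of 1² + (0.8/2)² = 1.16, an SD of 1.077 mm. Results are given for both SDs.

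**Chance of a non-significant result when the techniques truly differ** (54 vs 54, two-sided 0.05, *t* test).
- SE = SD × √(2/54) = 0.192 (SD 1) or 0.207 (SD 1.077).
- True 0.5 mm, SD 1: 0.5/0.192 = 2.60; power 0.731; non-significant 27%.
- True 0.5 mm, SD 1.077: 0.5/0.207 = 2.41; power 0.667; non-significant 33%.
- Smaller true differences at SD 1: 0.4 mm, 46%; 0.3 mm, 66%.

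The 95% interval for the technique difference has a half-width of about 0.38 mm at SD 1.

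**What a proper similarity test could show at this size.** For two one-sided tests at 5% with a true difference of zero, power ≈ 2Φ(M/SE − 1.645) − 1. For M = 0.5 and SD 1: 2Φ(2.60 − 1.645) − 1 = 0.66, or 0.65 with the *t* distribution. The protocol states no margin, so every M below is assumed.

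| Assumed margin | Power, SD 1 | Power, SD 1.077 |
|---|---|---|
| 0.4 mm | about 33% | about 22% |
| 0.5 mm | about 65% | about 55% |
| 0.6 mm | about 86% | about 78% |
| 0.8 mm | about 99% | about 97% |

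For 90% power at a 0.5 mm margin and SD 1, the need is 2(1.645 + 1.645)²/0.25 = 86.6, so 87 evaluable per pooled arm against 54.

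**The case against.** The strongest reply is that the protocol never says a non-significant P value will be taken as equivalence. The abstract's sentence is conditional, the Discussion speaks of exploring, and the stated goals are to compare and evaluate. This stands: the misuse is an inference. It does not remove the mismatch, because the hypothesis and the foreseen conclusion are on the page and none of the planned tests could support them. For the same reason, leaving detail to a statistical analysis plan is a weak defence. The tests are not omitted here; they are fixed, and of the wrong kind for this claim.

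Four stronger readings are tempting, and the document does not support them.
- *Both primary hypotheses claim similarity.* The second says that treatment with or without grafting can reach ideal results. That concerns each approach, not sameness, and the grafting contrast is sized to detect 0.8 mm.
- *The sample size rests on 0.5 mm and so contradicts similarity.* The 27 reproduces only from 0.8 mm. Citing 0.5 mm sits awkwardly beside a hypothesis of similarity, but the protocol does not say which technique it favours or whether 0.5 mm matters clinically.
- *The whole first hypothesis is unanswerable.* Its discomfort half is a superiority claim, which a difference test suits.
- *The chance of missing a survival difference can be quantified.* The protocol gives no expected survival rates, so any such figure would rest on assumed ones.

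**Conclusion.** The point holds for the technique contrast only. As written, the plan cannot support a conclusion that modified and traditional TSFE are similar, equivalent or the same in clinical effect. If non-significance were used for that purpose, a true 0.5 mm difference in bone remodeling would pass as similarity about 27% to 33% of the time. Those figures assume 54 evaluable per side, an SD of 1 to 1.077 mm and a two-sided 5% test; the upper one also assumes the full 0.8 mm grafting effect with no adjustment for it. The mismatch itself depends on none of these numbers.

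It should be settled before unblinding, since a margin chosen after the results are seen would not be credible.

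**What to change.** Before unblinding, do one of the following.

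(a) Pre-specify a justified equivalence or non-inferiority margin for technique, on bone remodeling at one named scheduled radiograph (week 26 or week 52, the sponsor's choice). For equivalence, claim similarity only if the 90% confidence interval for groups 1 + 2 against 3 + 4 lies wholly inside the margin (two one-sided tests at 5%). State the power that the current size gives for that margin.

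(b) If no margin can be justified, remove the words similar, equivalent and same from the planned conclusions, and report technique differences with 95% confidence intervals.

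Under either option, report the difference in implant survival with its 95% confidence interval and make no equivalence claim for it. The tests for discomfort and for grafting need no change on this account.

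The cost is a revision of the hypothesis wording and the analysis section. An equivalence conclusion becomes harder to reach, and margins of about 0.5 mm or less would be clearly underpowered at the current size. No extra enrolment is requested.

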## Methods/Design

### Overview

The proposed study is designed as a prospective single-center, four-arm parallel group, randomized controlled trial. We plan to recruit 120 patients who are in need of dental implant treatment in the atrophied posterior maxilla. The participants will be recruited by the research staff from Peking University Hospital of Stomatology First Clinical Division (Beijing, China). All interventions, follow-ups, and assessments will also be performed at this location. The study has been approved by the ethics committee of the Peking University School and Hospital of Stomatology (PKUSSIRB-201733019). The study has been registered in ClinicalTrials.gov under identifier number NCT03445039.

The systemic health condition and oral health condition of all participants will be recorded and inspected prior to surgery. All patients joining the study will receive standard oral hygiene maintenance instructions before implant surgery. Panoramic and cone beam computed tomography (CT) scan will be taken to assess the initial bone height, bone quality, and bone width.

### Inclusion criteria

1. The participant must be more than 18 years of age.2. The participant must have lost a single tooth or several teeth in the posterior area of the maxilla, where the tooth/teeth has/have been extracted for more than 3 months.3. The residual bone height of each participant is between 3 and 6 mm.4. The width of the alveolar ridge of each participant must be capable of containing an implant with standard diameter.5. The general and local status of the participant must be deemed suitable for implant placement and sinus floor elevation.6. The participant must be willing to sign an informed consent form and follow the rules in regard to follow-ups of the study.

### Exclusion criteria

1. Participants must not have uncontrolled systemic diseases, such as diabetes and hypertension.2. Participants must not have uncontrolled local diseases, such as periodontal disease or muco-cutaneous disease.3. Participants must not be a heavy smoker (smoking more than 10 cigarettes per day).4. Participants with rhinitis, sinusitis or rather large cyst in the maxillary sinus will be excluded from the study.5. The bone density of the maxillary posterior region of each participant must be strong enough to maintain the initial stability of the implant.6. Participants must not have previous implant treatment or bone grafting in the target implant site.7. Participants must not be in a state of mental illness or otherwise incapable of understanding and obeying the doctors’ instruction.

### Recruitment

Recruitment will take place in the Peking University Hospital of Stomatology First Clinical Division. Patients who are willing to join the clinical trial will receive the study information and consent forms. The consent forms must be signed before each patient is included in the present study. Figure 1 shows the flow of participants through the trial.

**Fig. 1 Fig1:**
[figure not shown]
Consolidated Standards of Reporting Trials (CONSORT) diagram of participant flow. Abbreviations: *MTSFE* modified transalveolar sinus floor elevation, *RFA* resonance frequency analysis, *TTSFE* traditional transalveolar sinus floor elevation, *VAS* visual analog scale

### Groups, randomization, and blinding

By means of randomization tables, all patients will be assigned to one the following four groups: (1) TSFE using osteotomes with bone grafting, (2) TSFE using osteotomes without bone grafting, (3) modified TSFE with bone grafting, or (4) modified TSFE without bone grafting. To ensure the blinding, the surgeon will not partake in the statistical analysis. On the other hand, the surgical plan and grouping will be confidential to the statistical analyst. Figure 1 shows the flow of participants through the trial.

### Surgical procedures

Implant and bone substitute: All the patients will receive the Straumann TE implants with SLA surface (Straumann AG, Basel, Switzerland). The bone substitutes are Deproteinized Bovine Bone Mineral (Bio-oss^®^, Geistlich, Wolhusen, Switzerland) and Deproteinized Bovine Bone Mineral with Porcine collagen (Bio-oss collagen^®^, Geistlich).

### Surgical interventions

For the traditional TSFE, the surgical procedure will be in accordance with the modified Summers’s method which was described by Pjetursson in 2009 [15], and the implant placement procedure will be in accordance with the product description by Straumann AG. The specific procedures are listed as below: the implant bed is prepared with the conventional steps. First, the alveolar ridge will be prepared with the Φ2mm round bur. Then, the Φ2.2 mm pilot drill will be used to ensure the direction and the insertion depth of the implants. The twist drills with Φ2.8 mm, 3.5 mm, and 4.2 mm will be used to enlarge the sockets separately (the diameter of the final drill is determined by the width of the implant). The drills will be stopped at 1–2 mm under the sinus floor. The socket preparation procedures will be irrigated by the 4 °C saline solution to reduce chances ofosteonecrosis which may result from the drill overheating. After that, the Φ2.2 mm osteotome with a concave head will be placed into the socket and the head of the osteotome will be knocked into the sinus cavity about 1 mm. The Φ2.8 mm osteotome then will be placed and knocked in to the sinus just about 1 mm less than the designed length. Finally, the Φ3.5 mm or Φ4.1 mm osteotome will be placed and knocked in to elevate the membrane to the ideal position. Prior to the filling of the bone substitute and implant placement, the sinus membrane will be tested for any perforations by the Valsalva maneuver (nose blowing test). If any air leaked through the implant site, it would have to be assumed that the sinus membrane was perforated; thus, the patient will be dropped from the current study. The patient will receive the appropriate therapy when the membrane is healed.

For the modified TSFE, the sinus lift procedure will be performed by the Dentium Advanced Sinus Kit (DASK) drills from Dentium Corporation (Cypress, CA, USA). After the preparation of the implant bed by the twist drills, the residual cortical bone will be elevated or grinded by the DASK #1 and #2 drills gently with minimum pressure. Then, the sinus membrane will be separated and elevated by the #3 drill. With the internal irrigation, the elevation procedure could be assisted by the water pressure. When the membrane is elevated with enough height, the bone substitute will be filled into the cavity and the implant will be placed. As with the traditional TSFE group, the Valsalva maneuver will be performed prior to the bone substitute filling and implant placement to test for any membrane perforation [13]. For the randomly selected control groups that are deemed not to require bone grafting, the implants will be inserted after the implant site preparation and sinus lift.

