### Measurement

#### Baseline measurement

The implant stability will be monitored by means of resonance frequency analysis (Osstell mentor; Integration Diagnostics AB, Göteborg, Sweden) immediately after surgery. After the implant placement, the implant stability will be tested by the Osstell Mentor in four directions (buccal, palatal, mesial, and distal). If the implant is deemed unable to maintain initial stability, the patient will be excluded from the current trial. The peri-apical radiographs and cone beam CT examination will be taken after the surgery. These digital radiographic data will be used as the baseline radiographic data.

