### Secondary parameters

The secondary parameters of this study include the following:1. VAS scale to evaluate pain, swelling, or bleeding after the surgery or a combination of these.2. Complications during and after the surgery which including infection, hematoma, nasal bleeding, and BPPV.3. Mucosal condition around the implant: The parameters include depth of probing, sulcus bleeding (by modified sulcus bleeding index), plaque around the restorations (by modified plaque index) will be documented. And the occurrence of biological complications (peri-implantitis and peri-implant mucositis) will be recorded.

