### Missing data

The possibility of loss to follow-up was considered and calculated as a part of the study’s sample size estimation. Otherwise, we will account for other types of randomly missing data by treating dropouts as non-success or non-survival using the intention-to-treat principle.

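### Patients are removed after randomisation for membrane perforation or lack of initial stability, so the technique comparison is conditioned on events that may differ by arm, and the intention-to-treat rule is not reconciled with this.

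*Protocol article*

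**What the plan says.** All references are to the protocol article.

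- **Allocation** (Groups, randomization, and blinding): "By means of randomization tables, all patients will be assigned to one the following four groups". The group fixes both the elevation technique and the use of graft.
- **Perforation, osteotome procedure** (Surgical interventions): after elevation a Valsalva test is done, and on an air leak "it would have to be assumed that the sinus membrane was perforated; thus, the patient will be dropped from the current study".
- **Perforation, modified procedure** (same section): "As with the traditional TSFE group, the Valsalva maneuver will be performed prior to the bone substitute filling and implant placement". What follows a positive test is not restated.
- **Initial stability** (Baseline measurement): "If the implant is deemed unable to maintain initial stability, the patient will be excluded from the current trial". This comes after placement and applies to all groups.
- **Primary parameters**: "The primary parameters of the current trial are implant survival rate, implant stability, and the bone remodeling around the implant".
- **Complications** (Secondary parameters): "Complications during and after the surgery which including infection, hematoma, nasal bleeding, and BPPV". Perforation is not named.
- **Missing data**: data that are missing randomly are handled by "treating dropouts as non-success or non-survival using the intention-to-treat principle".
- **Link to technique** (Background): "Some studies reported a relatively high incidence of sinus membrane perforations when TSFE is performed". The section adds that modified procedures were proposed partly to reduce perforation, and that the non-cutting drills are shaped to spare the membrane.
- **Sample size**: 27 per group, raised to 30 for about 10% loss to follow-up.

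**The concern.** A patient can perforate only once the allocated instruments have been used, and can lack initial stability only once the implant is in. Neither is an eligibility check made before allocation. If such patients leave the trial, the techniques are compared in those whose surgery went well, and the protocol itself gives reason to expect that perforation, at least, differs between techniques.

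The first primary hypothesis is that the modified technique gives clinical results similar to the traditional one. Removing technique-related failures from both arms can produce similarity that randomisation did not. If the drills perforate less often, that advantage drops out of the survival comparison; if more often, the disadvantage does.

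Lack of initial stability touches a primary parameter directly: the patients removed are presumably at the low end of the baseline stability readings.

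The documents also leave two readings of the same patient. Under Surgical interventions a perforated patient is absent from the trial. Under Missing data a dropout is a failure. An analyst could follow either.

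**Working it through.** **1. The plan's own figure.** Inputs from Sample size: difference 0.8 mm, SD 1 mm, alpha 0.05, power 90%.

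n = 2 × (1.645 + 1.282)² × 1² / 0.8² = 26.8, so 27 per group. Then 27 / 0.9 = 30, and 4 × 30 = 120.

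This reproduces the stated 27, 30 and 120, but only with a one-sided alpha, which the protocol does not state (two-sided gives 33). That is a separate matter. What counts here is that the 10% allowance is tied to loss to follow-up and includes nothing for perforation or lack of stability.

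**2. Order of events.** Randomise to a technique and graft group → prepare and elevate with the allocated instruments → Valsalva test (drop if positive) → graft if allocated, place implant → stability test (exclude if inadequate) → follow-up. Both removals come after allocation.

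**3. Effect on the survival comparison.** The documents give no perforation or instability rates, so the following are assumptions.

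- Randomised per technique: 2 × 30 = 60.
- Survival among retained patients: s = 97% in both techniques.
- Proportion removed: pO with osteotomes, pM with drills, with the same rule applied to both.

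If removed patients are dropped, both techniques show s, and the difference is 0 by construction. If they count as non-success, success is (1 − p) × s, and the difference (modified minus osteotome) is s × (pO − pM).

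| pO vs pM | Dropped | Counted as non-success | Difference (points) |
|---|---|---|---|
| 5% vs 2% | 97% vs 97% | 92.2% vs 95.1% | 2.9 |
| 10% vs 3% | 97% vs 97% | 87.3% vs 94.1% | 6.8 |
| 10% vs 10% | 97% vs 97% | 87.3% vs 87.3% | 0 |
| 20% vs 5% | 97% vs 97% | 77.6% vs 92.2% | 14.6 |
| 5% vs 10% | 97% vs 97% | 92.2% vs 87.3% | −4.9 |

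For the second row: 0.90 × 0.97 = 0.873 and 0.97 × 0.97 = 0.941. Of 60 per technique, 6 and about 2 patients would be removed.

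**4. Effect on numbers.** Evaluable per group = 30 × 0.9 × (1 − p). This gives 27.0 at p = 0, 25.7 at 5%, 24.3 at 10% and 21.6 at 20%. One-sided power for 0.8 mm between two single groups goes from 90.2% to 88.9%, 87.4% and 83.7%.

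The factor comparisons in Statistical analysis pool two groups per side. At p = 10% each side has 2 × 24.3 = 48.6, and two-sided power for 0.8 mm is Φ(0.8 × √(48.6/2) − 1.96) = Φ(1.98), about 98%. For the 0.5 mm technique difference it is 69%, against 74% with 54 per side.

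**The case against.** **The rules may already agree.** Surgical interventions says patients are dropped, and Missing data counts dropouts as non-success. Read together, a perforated patient may already be a failure. This stands in part: the text is unreconciled rather than flatly contradictory. It does not settle the matter, because the Missing data rule is written for randomly missing data, which these cases are not, and the other two sections speak of removal from the study or trial.

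**Initial stability is partly about eligibility.** Item 5 of the Exclusion criteria requires bone dense enough to hold the implant, so the later exclusion can be read as confirming this at surgery. That stands. A reader might infer that both exclusions remove failures caused by technique, but nothing in the documents ties initial stability to technique. What remains is that the exclusion follows randomisation and touches a primary parameter.

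**Perforation may be recorded anyway.** The complication list is open-ended and covers events during surgery, every patient is tested, and the flow diagram is not shown. So it cannot be said that perforation will go unreported, only that it is not a named outcome.

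**The sample is not necessarily too small.** A reader might infer from 24.3 against 27 that the trial falls short. The pooled comparisons retain ample power for 0.8 mm, and the weakness for 0.5 mm exists without any exclusions. The inference does not hold as a general claim.

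**The illustration would rarely reach significance.** At 87.3% vs 94.1% with 60 per technique, power is about 25%. True, but the hypothesis is similarity, so the concern is a biased estimate rather than a missed P value.

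**Conclusion.** The point holds for the analysis population. Followed as written, Surgical interventions and Baseline measurement make the comparison of groups 1+2 with 3+4 conditional on what happened after randomisation. The bias argument is strong for perforation, which the protocol links to technique, and limited for initial stability.

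The Missing data section does not clearly bring these patients back. The modified procedure repeats the test without saying what a positive result leads to, so equal handling of the two techniques is implied but not fixed; unequal handling would be worse.

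Size and direction are unknown. Under the assumed rates with more osteotome exclusions, dropping patients would conceal about 3 to 15 percentage points in favour of the drills. With equal rates it conceals no difference, and with more drill exclusions the sign reverses. These figures rest on 97% survival among retained patients in both techniques. Loss of power is a minor part of the problem.

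**What to change.** Leave clinical care as it is and change the analysis text:

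1. Reconcile Surgical interventions (both procedures), Baseline measurement and Missing data, so that all randomised patients in both techniques stay in the analysis set whatever happens at surgery.
2. Name perforation and lack of initial stability as outcomes, and report both by randomised arm.
3. Analyse survival or success in all randomised patients, extending the Missing data rule explicitly to these cases. Show survival among implanted patients alongside; the two answer different questions and both are useful.
4. Label bone remodeling and implant stability results as conditional on implantation, since they cannot be measured where no implant was placed.
5. State that the 10% in Sample size covers loss to follow-up only.

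The cost is a wording change, one more field on the surgery form, and survival figures that may look less favourable. The trial status is open for recruitment, so this can still be done before analysis. No change to how or when the graft allocation is disclosed is needed.
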